### **3.3 Exclusion criteria**

1. Patients already receiving pregabalin or gabapentin, irrespective of indication, at the time of screening.
2. Known hypersensitivity to pregabalin or gabapentin or their components.
3. Pregnancy or breast feeding.

### **3.4 Study design:**

The study is designed as a randomized double-blind placebo-controlled trial. All patients will sign a written informed consent. Randomization will be done using computer generated blocks. There will be no stratification factors. An independent biostatistician will perform the randomization. Pregabalin and matching placebo will be dispensed to the patient by a designated person, who is not a member of the study team. The investigators, research staff and the patients will be masked to the study arm and will have no access to the randomization schedule. Patients will be randomized to one of the following 2 arms:

Arm A: Pregabalin starting at 75 mg orally daily, with dose escalation over 7 days (according to dose escalation schedule) to a maximum dose of 300 mg orally daily for 9 weeks followed by de-escalation over 7 days, then stop; or

Arm B: Placebo, with dose escalation over 7 days (according to dose escalation schedule), followed by the maximal dose for 9 weeks followed by de-escalation over 7 days, then stop.

### **3.5 Dose escalation schedule:**

Pregabalin or placebo will be started from the day of randomization and the dose will be escalated provided the patient is not experiencing excess toxicity as per the dose escalation schedule described in the table given below. Once dose escalation is completed, pregabalin 300 mg or placebo orally daily will be continued until 9 weeks, i.e. until the first restaging imaging study is performed. After efficacy assessment is completed, pregabalin or the placebo will be tapered (again according to the protocol) over 6 days and then discontinued.

| **Phase** | **Days** | **Daily dose (mg)** | **Schedule (1 capsule=75 mg)** |
| --- | --- | --- | --- |
| Escalation | 1-2 | 75 | 1 capsule, morning |
|  | 3-4 | 150 | 1 capsule, morning and evening |
|  | 5-6 | 225 | 1 capsule, morning, midday and evening |
| Maximal treatment | 7 days to 9 weeks | 300 | 1 capsule, morning and midday;  2 capsules, evening |
| Reduction (start after week 9, once efficacy has been assessed); day numbers counted from the date of assessment of efficacy. | 1-2 | 225 | 1 capsule, morning, midday and evening |
|  | 3-4 | 150 | 1 capsule, morning and evening |
|  | 5-6 | 75 | 1 capsule, morning |
|  | 7 | 0 | Stop |

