As per the product label, the most common adverse events (> 5%) include giddiness, somnolence, dry mouth, peripheral edema, blurred vision, weight gain and cognitive impairment/thinking abnormalities, especially abnormalities with thinking/concentration. Although rare and not reported in the trial in which pregabalin was used for the management of refractory cough, pregabalin may lead to the following severe side-effects

- Angioedema: swelling of the throat, head and neck, which may progress to life-threatening respiratory compromise. Pregabalin should be immediately discontinued.
- Hypersensitivity reactions, like urticaria, wheezing and dyspnea. Pregabalin should be immediately discontinued.
- Increased seizure frequency may occur in patients with seizure disorders, if pregabalin is withdrawn rapidly. Pregabalin must be tapered over 1 week according to the schedule in the protocol
- Pregabalin may cause giddiness and somnolence. Patients should be warned not to drive or operate heavy machinery, while on pregabalin.
  1. **Dose modifications of pregabalin**: Pregabalin is primarily excreted renally. If the patient develops renal impairment (based on the calculated glomerular filtration rate, using the Cockcroft-Gault formula), while on pregabalin, the dose should be modified, based on the calculated creatinine clearance, as follows:

| **Creatinine clearance in ml/min** | **Total pregabalin daily dose (maximal)** |
| --- | --- |
| >60 | 300 |
| 30 to 60 | 150 |
| 15 to 30 | 75 |
| < 15 | 25 – 50 |

In patients who are not tolerating pregabalin due to any intolerable side-effect, the dose of pregabalin should be decreased by 1 step (as per the dose escalation schedule), and this lower dose should be continued for 3 days. If the patient is able to tolerate the lower dose, this should be continued for the duration of the study. If the patient continues to have intolerable side-effects at the lower dose level, the dose of pregabalin may be further reduced, as per the dose escalation table.

Intolerable side-effects of pregabalin will include:

1. Dizziness, grade 3 (severe unsteadiness or sensation of movement; limiting self-care activities of daily living) or any grade but reported intolerable by the patient.
2. Weight gain grade 3 (=/>20% from baseline), which is due to the study drug, and not due to patient responding to cancer-directed therapy with improvement in overall general condition.

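### The only taper schedule starts at 225 mg and, read literally, raises the dose of any patient maintained at 150 mg or below, including every patient under a reduced renal maximum

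*Protocol*

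**What the plan says.** **Taper.** The table in section 3.5 gives a single reduction phase: "Reduction (start after week 9, once efficacy has been assessed); day numbers counted from the date of assessment of efficacy". Its rows are 225 mg on days 1-2, 150 mg on days 3-4, 75 mg on days 5-6, and stop on day 7. The seizure warning in section 3.6 says that pregabalin has to be tapered over a week by the protocol's schedule. This is the only schedule there is.

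**Reduced doses.** The dose-modification paragraph of section 3.6 creates patients who reach the taper on less than 300 mg by two routes.

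- Intolerance: the dose drops one step of the escalation table. "If the patient is able to tolerate the lower dose, this should be continued for the duration of the study". Otherwise it may drop further.
- Renal impairment that develops on treatment: "the dose should be modified, based on the calculated creatinine clearance, as follows". The maximal daily doses are 300 mg (clearance above 60 ml/min), 150 mg (30 to 60), 75 mg (15 to 30) and 25-50 mg (below 15).

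**Duration.** Section 3.4 describes Arm B as a 7-day escalation "followed by the maximal dose for 9 weeks followed by de-escalation over 7 days, then stop". Section 3.5 says "Pregabalin or placebo will be started from the day of randomization" and then that "pregabalin 300 mg or placebo orally daily will be continued until 9 weeks, i.e. until the first restaging imaging study is performed". The cancer-directed therapy paragraph of section 3.6 also treats 9 weeks as the end of pregabalin.

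**Capsule.** The only unit described is a 75 mg capsule (column heading of the section 3.5 table).

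**The concern.** The reduction table is written for a patient who finishes on 300 mg. Section 3.6 foresees patients who do not, and it points back to the same table without an entry rule. A patient whose dose was lowered for intolerable side-effects or falling renal function could then be given more drug during the taper than while on maintenance. Section 3.4 has the drug dispensed by a designated person outside the study team, who would work from the written schedule.

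At stake are patient safety and uniform conduct in a phase that is part of the trial: completion includes stopping after the taper, and serious adverse events are reportable until two weeks after study drug ends. The duration and renal-table mismatches are smaller, but they sit in the same operative text and would be settled by the same amendment.

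**Working it through.** **1. The plan's own table.** Capsules × 75 mg: 1, 2, 3 and 4 capsules give 75, 150, 225 and 300 mg. The capsule counts and daily doses in section 3.5 agree, both going up and coming down.

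**2. Taper against maintained dose.** Change = taper-row dose − maintained dose, in mg. The 225 mg row comes from the escalation steps, 150 and 75 mg from the steps or the renal table, and 25-50 mg from the renal table only.

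| Maintained dose | Days 1-2 (225) | Days 3-4 (150) | Days 5-6 (75) | Days above maintained dose |
| --- | --- | --- | --- | --- |
| 300 | −75 | −150 | −225 | 0 |
| 225 | 0 | −75 | −150 | 0 |
| 150 | +75 | 0 | −75 | 2 |
| 75 | +150 | +75 | 0 | 4 |
| 50 | +175 | +100 | +25 | 6 |
| 25 | +200 | +125 | +50 | 6 |

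As ratios on days 1-2: 225/150 = 1.5 and 225/75 = 3. The reduced renal maxima are 150, 75 and 25-50 mg, and 225 mg exceeds each of them.

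**3. Time at the maximal dose.**

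- Section 3.4, Arm B: 9 × 7 = 63 days after a 7-day escalation, ending on day 7 + 63 = 70 (day 69 if the escalation takes six days, as in the table).
- Section 3.5: day 7 to the end of week 9 (day 63), that is 63 − 7 + 1 = 57 days.
- Difference: 63 − 57 = 6 days at full dose, or 70 − 63 = 7 days by end date.
- Visit window of 9 weeks ± 7 days: an assessment on day 56 or day 70 gives 56 − 7 + 1 = 50 or 70 − 7 + 1 = 64 days at 300 mg under section 3.5.

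**4. Renal rows against the capsule.** 300/75 = 4, 150/75 = 2 and 75/75 = 1, all whole capsules. 50/75 = 2/3 and 25/75 = 1/3 are not. A clearance of exactly 30 ml/min belongs to both the 150 mg and the 75 mg row.

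**The case against.** The best reply is that the words reduction, taper and de-escalation exclude an increase, so a sensible site would enter the table at the next lower row. That is probably what was meant. But no passage says so, and section 3.6 sends the reader to the table without qualification. The missing entry rule therefore stands as a fault, even if few sites would follow the table literally.

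Several stronger readings are tempting, and the protocol does not support them.

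- *Every reduced-dose patient is raised.* Not so. One step down is 225 mg, and that patient stays at 225 mg on taper days 1-2 and then falls. A rise needs at least two steps down or a renal cap.
- *The timing of the primary assessment is unclear.* It is fixed at 9 weeks (± 7 days) from randomization in section 3.6, and section 3.5 starts the taper only after it. What remains is a mismatch in the arm description. The Arm A sentence alone, "to a maximum dose of 300 mg orally daily for 9 weeks followed by de-escalation over 7 days, then stop", could even be read as 9 weeks in total; it is the Arm B sentence that clearly places 9 weeks after escalation. The visit window can hide the 6-day gap, but the two statements still differ.
- *A taper of 6 days contradicts one of 7.* This is a counting convention: doses on days 1-6, stop on day 7.
- *The lowest renal row endangers the blind or affects many patients.* Entry requires a clearance above 60 ml/min, so a fall below 15 within about 9 weeks should be rare. The column states maxima, and nothing shows that another strength would be unmatched.
- *The 45% dizziness rate cited from the earlier cough trial indicates how many patients are affected.* That figure is for all grades. Reduction requires grade 3 or intolerable dizziness, and one reduction alone causes no rise.

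**Conclusion.** The point holds for patients maintained at 150 mg or below. Read literally, the single reduction schedule lifts them to 225 mg on taper days 1-2: by 75 mg from 150 mg, and by 150 mg from 75 mg, where the dose is still 75 mg too high on days 3-4. It also exceeds every reduced renal maximum. This rests on taking the table as the schedule for all patients, which the text supports because it offers no other. The number of patients affected cannot be derived from the protocol.

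The secondary points are minor: 63 against about 57 days at the maximal dose, one renal row that whole 75 mg capsules cannot deliver, and a shared boundary at 30 ml/min. All of these are drafting contradictions in dosing text. None touches the primary time point, the sample size or the planned comparison. The point should be corrected because the first part concerns patient safety and is cheap to settle.

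**What to change.** The sponsor should reconcile three sets of passages.

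1. The reduction table in section 3.5 with the intolerance and renal rules in section 3.6, so that the protocol states how the taper applies to a patient on a reduced dose.
2. The arm descriptions in section 3.4 with section 3.5 and with the assessment and cancer-directed therapy paragraphs of section 3.6, so that one treatment duration is given, counted from one stated origin.
3. The lowest renal row with the capsule described, and the two rows that share a clearance of 30 ml/min.

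Which dose or rule is right is for the sponsor to decide; none is proposed here. The cost is a protocol amendment and matching dispensing instructions, with no extra patients, visits or analyses.

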### 3.6 **Study procedures**

Persons being evaluated for lung cancer in the thoracic medical oncology outpatient department at Tata Memorial Hospital will be questioned about the presence and severity of cough. Patients with cough will be assessed for eligibility. If found eligible and willing to participate in the trial, written informed consent will be obtained. The patient will then be randomized by computer generated blocks to either Arm A (pregabalin 300 mg orally daily) or Arm B (placebo). Investigators, research staff and the patients will be blinded to the study arm. Baseline laboratory tests performed within a week from the date of randomization to assess organ function i.e., complete hemogram, liver and renal function tests and serum electrolytes (sodium, potassium, magnesium, calcium) will be accepted. Evaluation of the performance status and physical examination will be performed by the treating physician. Pulse and blood pressure will be recorded at baseline and every visit.

Information regarding medications that the patient is taking, including additional antitussive medications will be recorded. Plan for oncologic therapy will also be noted.

Tools for assessing cough severity (VAS, MCLCS) will be administered at baseline, on day 7 (+/- 3 days) and 9 weeks (+/- 7 days) from randomization. In patients who are unable to fill out the questionnaires on their own or have trouble reading, the research staff or social workers will help them.

QoL will be assessed using EORCTC QLQ-Q30 and LC13 questionnaires for lung cancer at baseline, day 7 (+/- 3 days) and 9 weeks (+/- 7 days). In patients who are unable to fill out the questionnaires on their own or have trouble reading, the research staff or social workers will help them.

Toxicity data will be recorded and treated as appropriate. The side-effects will be graded according to the Common Terminology Criteria for Adverse Events (CTCAE) v.5. Detailed description of anticipated toxicity and frequency from pregabalin is provided in the next section on adverse events.

- 1. **Adverse events of pregabalin**: In the phase II study evaluating the role of pregabalin and speech pathology combination therapy for patients with chronic refractory cough, the most frequently noted side-effects (all grades) that occurred more commonly with pregabalin as compared to placebo included dizziness (45%), weight gain (25%), blurred vision (20%) and cognitive changes (30%) (13).

As per the product label, the most common adverse events (> 5%) include giddiness, somnolence, dry mouth, peripheral edema, blurred vision, weight gain and cognitive impairment/thinking abnormalities, especially abnormalities with thinking/concentration. Although rare and not reported in the trial in which pregabalin was used for the management of refractory cough, pregabalin may lead to the following severe side-effects

- Angioedema: swelling of the throat, head and neck, which may progress to life-threatening respiratory compromise. Pregabalin should be immediately discontinued.
- Hypersensitivity reactions, like urticaria, wheezing and dyspnea. Pregabalin should be immediately discontinued.
- Increased seizure frequency may occur in patients with seizure disorders, if pregabalin is withdrawn rapidly. Pregabalin must be tapered over 1 week according to the schedule in the protocol
- Pregabalin may cause giddiness and somnolence. Patients should be warned not to drive or operate heavy machinery, while on pregabalin.
  1. **Dose modifications of pregabalin**: Pregabalin is primarily excreted renally. If the patient develops renal impairment (based on the calculated glomerular filtration rate, using the Cockcroft-Gault formula), while on pregabalin, the dose should be modified, based on the calculated creatinine clearance, as follows:

| **Creatinine clearance in ml/min** | **Total pregabalin daily dose (maximal)** |
| --- | --- |
| >60 | 300 |
| 30 to 60 | 150 |
| 15 to 30 | 75 |
| < 15 | 25 – 50 |

In patients who are not tolerating pregabalin due to any intolerable side-effect, the dose of pregabalin should be decreased by 1 step (as per the dose escalation schedule), and this lower dose should be continued for 3 days. If the patient is able to tolerate the lower dose, this should be continued for the duration of the study. If the patient continues to have intolerable side-effects at the lower dose level, the dose of pregabalin may be further reduced, as per the dose escalation table.

Intolerable side-effects of pregabalin will include:

1. Dizziness, grade 3 (severe unsteadiness or sensation of movement; limiting self-care activities of daily living) or any grade but reported intolerable by the patient.
2. Weight gain grade 3 (=/>20% from baseline), which is due to the study drug, and not due to patient responding to cancer-directed therapy with improvement in overall general condition.
3. Blurred vision grade 3 (symptomatic with marked decrease in visual acuity; best corrected visual acuity worse than 20/40 or more than 3 lines of decreased vision from known baseline, up to 20/200; limiting self-care activities of daily living)
4. Cognitive disturbance grade 3 (severe cognitive disability; significant impairment of work/school/life performance)
5. Any other side-effect, which is reported to be intolerable by the patient, and is attributed to the study drug by the investigator.
   1. **Additional medications**: For all patients on either arm, additional cough medications will be added stepwise according the list given below. First, an antitussive should be ordered from the ‘a’ group. In case the patient reports that the cough is not improved after at least 3 days of using the antitussive medication form group ‘1’, this should be stopped and an antitussive from the group ‘2’ should be started, and so on.
6. Expectorant/mucolytic (guaifenesin/bromhexine)
7. Antihistamine (diphenhydramine/chlorpheniramine)
8. Adrenergic blocker (phenylephrine/terbutaline)
9. Narcotic derivative (codeine, dextromethorphan)

Examples of the commercially available cough medications in the various above categories is provided below.

| **Order of prescription** | **Class of antitussive** | **Commercially available cough medications** |
| --- | --- | --- |
| 1 | Expectorant/mucolytic | - Brozedex - Ascoril - Acticuf - Xpect-B |
| 2 | Antihistamine | - Benadryl - Coffdryl - Sinarest - Zedex |
| 3 | Adrenergic blocker | - Terbutaline - Asthalin |
| 4 | Narcotic derivative | - Corex - Alex - Coscopin - Grilinctus |

If patients require other medications while they are on study like corticosteroids (for brain or spinal cord metastases), antibiotics, bronchodilators and opioids (like morphine for pain) these will be permitted, and use will be documented.

- 1. **Cancer-directed therapy**: All patients will be started on cancer-directed therapy, as per the decision of the treating oncologist. The therapeutic regimen with the dose and frequency will be documented. Usually, the first restaging evaluation occurs after 3 cycles of chemotherapy, i.e. after 9 weeks, which will be the time of the end of pregabalin in the cough study.

Although the response of the patients to cancer-directed therapy will impact the cough, we hope that the number of responders to therapy will be roughly equally distributed between the two arms, and that this confounder will be taken care of by means of randomization.

- 1. **Completion of the trial:** The patient will be considered to have completed the trial if:
- Patient has completed the 9-week assessments and has discontinued pregabalin after dose taper
- Patient withdraws consent.
- The investigator feels that it not in the patient’s best interest to continue on the trial.

### **4. Adverse Events**

Information about all adverse events will be collected, recorded and followed up as appropriate. Grading of adverse events will be according to CTCAE v.5. An adverse event is any undesirable sign, symptom or medical condition occurring after starting study treatment, even if the event is not considered to be treatment-related.

Medical conditions/diseases present before starting study treatment will be only considered adverse events if they worsen after starting study treatment. Clinical events occurring before starting study treatment but after signing the informed consent form will be recorded on the Case Report Form. Abnormal laboratory values or test results will constitute adverse events only if they induce clinical signs or symptoms or require therapy and will be recorded on the Adverse Events Case Report Form under the signs, symptoms or diagnosis associated with them.

As far as possible, each adverse event will be described by:

1. its duration (start and end dates)
2. the severity grade- as per CTCAE v.5
3. its relationship to the study drug (suspected /not suspected),
4. the action(s) taken.

**4.1 Serious Adverse Event (SAE)**: Information about all serious adverse events will be collected and recorded on the SAE Report Form and will be reported to the independent ethics committee within 24 hours of learning of its occurrence. An SAE is defined in general as an untoward (unfavorable) event which is fatal or life-threatening, required or prolonged hospitalization, significantly or permanently disabling or incapacitating, may jeopardize the subject and may require medical or surgical intervention to prevent one of the outcomes listed above.

Events not considered to be SAEs are hospitalizations occurring under the following circumstances: were planned before entry into the clinical study; are for elective treatment of a condition unrelated to the studied indication or its treatment; occur on an emergency, outpatient basis and do not result in admission (unless fulfilling the criteria above); are part of the normal treatment or monitoring of the studied indication and not associated with any deterioration in condition.

Any SAE occurring after the patient has provided informed consent and until two weeks after the patient has completed study drug must be reported. This includes the period in which the study protocol interferes with the standard medical treatment given to a patient (e.g. treatment withdrawal during washout period, change in treatment to a fixed dose of concomitant medication). SAEs occurring more than two weeks after study drug discontinuation need only be reported if a relationship to the study drug (or therapy) is suspected.

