### Secondary objectives

1. To study the change in Manchester Cough in Lung Cancer Scale (MCLCS) scores between baseline and week 9 of treatment with pregabalin (at maximal tolerated dose of 300 mg per day) as compared to placebo.
2. To study the change in VAS and MCLCS scores between baseline and day 7 of treatment with pregabalin (at maximal tolerated dose of 300 mg per day) compared to placebo.
3. To study the effect of pregabalin (at maximal tolerated dose of 300 mg per day) versus placebo on improvement in quality of life (QOL) in lung cancer patients with chronic cough using EORTC QOL questionnaires.
4. To describe the adverse effects of pregabalin in lung cancer patients with chronic cough.

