### **3.2 Inclusion criteria**

1. Age 18 years or older.
2. Locally advanced or metastatic suspected or diagnosed NSCLC.
3. Eastern Cooperative Group performance status between 0 and 2.
4. Moderate (grade 2) or severe (grade 3) cough that has lasted for 2 or more weeks. Cough severity will be according to the Common Terminology Criteria for Adverse Events (CTCAE), v.5, in which grade 2 signifies moderate symptoms, medical intervention required, limiting instrumental activities of daily living; and grade 3 cough signifies severe symptoms limiting self-care activities of daily living.
5. Willing and able to limit to one alcoholic beverage per day (e.g. 360 ml of beer or 120 ml of wine or 330 ml of cooler or 43 ml of hard liquor like whisky/vodka/rum/gin).
6. Creatinine clearance measured by the Cockcroft-Gault formula > 60 ml/min.
7. Women of childbearing potential must be willing to consent to using effective contraception (e.g., hormonal contraceptives, bilateral tubal ligation, barrier with spermicide, intrauterine device) while on treatment and for at least 3 months thereafter. A man who is the partner of a woman of childbearing potential must be willing to consent to using effective contraception (e.g., vasectomy or barrier with spermicide) while on treatment and for 3 months thereafter.
8. Capable of providing informed consent and follow trial procedures.

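### The laboratory rule for adverse events does not list a change in study drug as a trigger, so a symptom-free, untreated fall in creatinine clearance that cuts the dose may go unrecorded as an adverse event

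*Protocol*

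**What the plan says.** Protocol section 4 begins with a general definition: "An adverse event is any undesirable sign, symptom or medical condition occurring after starting study treatment". It then gives a specific rule for laboratory findings: "Abnormal laboratory values or test results will constitute adverse events only if they induce clinical signs or symptoms or require therapy". Findings that qualify "will be recorded on the Adverse Events Case Report Form under the signs, symptoms or diagnosis associated with them". Duration, CTCAE grade, relationship to study drug and action taken are listed in the same section as descriptors of each adverse event.

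The dose-modification text in section 3.6 begins its renal rule with "If the patient develops renal impairment", judged by the Cockcroft-Gault calculation, and continues: "while on pregabalin, the dose should be modified, based on the calculated creatinine clearance". A table of maximal daily doses by clearance band follows. Inclusion criterion 6 in section 3.2 requires "Creatinine clearance measured by the Cockcroft-Gault formula > 60 ml/min".

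On reporting, secondary objective 4 is "To describe the adverse effects of pregabalin in lung cancer patients with chronic cough". Section 3.6 adds: "Toxicity data will be recorded and treated as appropriate". Section 5.2 presents adverse events as percentages and compares toxicities between arms by a chi-square or Fisher test.

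**The concern.** Section 3.6 makes a calculated laboratory value sufficient to change study drug. The laboratory sentence in section 4 makes a laboratory value an adverse event on two conditions only, and a change in study drug is neither of them. Staff who follow both sections to the letter could lower a patient's dose for a silent fall in clearance and open no adverse event entry.

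The descriptors in section 4 belong to an adverse event. Without an entry, that section gives no place for the grade, the relationship judgement or the action taken. The adverse event percentages, and with them the description promised by secondary objective 4, could then omit some laboratory events that altered treatment. What section 4 admits also governs data capture: an analysis plan written later cannot tabulate adverse events that were never entered.

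**Working it through.** The point rests mainly on definitions, so the provisions are set side by side first.

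**Step 1. What triggers a dose reduction.** Section 3.6 has two routes.
- Intolerable side-effects: dizziness, weight gain, blurred vision, cognitive disturbance, or another effect the patient reports as intolerable. Each is a sign or symptom and meets the general definition in section 4.
- Calculated creatinine clearance. This is derived from a laboratory value, and no symptom is required.

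The second route is the only one for which an adverse event entry is not assured.

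**Step 2. Which clearance falls qualify under section 4.**

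| Fall in clearance | Adverse event under section 4? |
| --- | --- |
| Causes signs or symptoms | Yes, laboratory sentence |
| Needs therapy | Yes, laboratory sentence |
| Recorded as the condition renal impairment | Arguably, general definition |
| Symptom-free, untreated, seen only as a number, dose reduced | Not under the laboratory sentence |

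The last row is the gap. Reducing study drug is not naturally read as therapy for the abnormality, and section 4 lists action taken as a separate descriptor.

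**Step 3. Size of the dose change.** The entry criterion places every patient in the 300 mg row at baseline. The inputs are the doses in the renal table of section 3.6. The reduction in maximal daily dose is 100 × (1 − dose/300):
- 30 to 60 ml/min, 150 mg: 100 × (1 − 150/300) = 50%
- 15 to 30 ml/min, 75 mg: 100 × (1 − 75/300) = 75%
- below 15 ml/min, 50 mg: 100 × (1 − 50/300) = 83%
- below 15 ml/min, 25 mg: 100 × (1 − 25/300) = 92%

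These are cuts in the permitted maximum. A patient already reduced for tolerability loses less: from 225 mg to 150 mg is 100 × (1 − 150/225) = 33%.

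**Step 4. Number of patients affected.** This cannot be calculated. The protocol gives no rate of renal impairment. The only laboratory tests section 3.6 names are at baseline, so the number of silent falls that would be detected is also unknown.

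**The case against.** The strongest reply is that the two sections answer different questions. The renal table exists because pregabalin is cleared by the kidney, so it adjusts exposure and does not call the fall in clearance a toxicity. Section 4 decides what is recorded as an adverse event. Both can be obeyed at once, and restricting laboratory adverse events to those with clinical consequence is a coherent rule. This stands. A reader might infer a direct contradiction, but the text supports only a gap between the two.

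Second, an investigator may record renal impairment as a medical condition or diagnosis. This stands in part. The general definition leaves that route open, but the laboratory sentence is the specific rule and is worded restrictively. The reference to a diagnosis says where qualifying findings are entered and does not add a way to qualify. Two sites of judgement could therefore code the same event differently.

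Third, a reader might infer that such events necessarily drop out of the toxicity comparison. The documents do not say so: sections 3.6 and 5.2 speak of toxicity without tying the word to the laboratory rule, and the choice of events for safety tables is often left to the analysis plan. The link to the adverse event percentages is firmer, because section 5.2 uses the term that section 4 defines.

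Fourth, nothing in the protocol shows that dose changes or their reasons go unrecorded elsewhere. The case report forms are not shown, so it cannot be claimed that a reduced dose would have no documented reason. Finally, renal decline is not among the adverse effects the protocol anticipates for pregabalin, which limits the consequence for secondary objective 4.

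**Conclusion.** The point holds in a limited form. As section 4 is worded, a fall in clearance that is symptom-free, untreated and not entered as a diagnosis may go unrecorded as an adverse event even though it lowers the maximal daily dose by 50%, 75%, or 83% to 92%. It may then be absent from the adverse event percentages and possibly from the toxicity comparison.

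A reader might go further and conclude that any dose-cutting fall in clearance is excluded, or might put a count on the lost events. Neither is supported. Falls with symptoms or treatment do qualify. Any count would need an assumed rate of renal impairment, an assumed share that is silent and uncoded, and an assumed testing schedule, none of which the protocol gives.

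The conclusion rests on two readings: that reducing study drug is not therapy, and that the specific laboratory sentence takes precedence over the general definition. The primary VAS analysis and the sample size are not affected. Cheap improvement.

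**What to change.** Reconcile section 4 with the renal rule in section 3.6 by adding a third trigger to the laboratory sentence: *or lead to a reduction, interruption or stop of study drug*. Apply it identically in both arms, under blinding, so that placebo patients whose capsules are changed by the same table are recorded in the same way. State that these events carry CTCAE grade, relationship and action taken, and that they enter both the adverse event summary and the toxicity comparison in section 5.2.

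The cost is one clause and what should be a small number of extra adverse event entries. No test or visit is added, and no dose or clinical rule changes.
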